**Fig. 1 Fig1:**
[figure not shown]
Flow chart of study. Note: FC-SBD= Family Connections for Suicidal Behavior Disorder; TAU-O = Treatment at Usual Optimized

### Sample size

The sample size for this study was generated from effect sizes found in other studies with relatives of people with mental disorders. In the literature, we found a controlled study by Grenyer et al. [22] on a psychoeducational group intervention protocol for family members of people with borderline personality disorder. On the one hand, they found medium to large effect sizes for dyadic adjustment (d=0.78) and family empowerment (d=1.4); on the other hand, they found medium effect sizes for burden (d=0.45) at post-test and 12-month follow-up. The results of these effect sizes are consistent with other studies on psychological treatments for other mental disorders, such as a meta-analysis by Baruch, Pistrang and Barker [34] on psychological interventions for bipolar disorder (Burden, g = -.80). Based on the results of these studies, we expect an effect size of 0.60 because the design of this study consists of two experimental groups. For the calculation of the sample size, we used the G*Power 3.1 software [35], taking into account an alpha of 0.05 and a statistical power of 0.80 in a two-tailed t-test. We need a sample size of 90 participants (45 relatives per condition) to reach an effect size of 0.60 for burden. Finally, we considered possible sample loss during the treatment program. Based on studies of interventions for relatives of people with borderline personality disorder, we expect a 30% dropout rate [17, 23, 27, 36, 37]. Therefore, taking this outcome into account, our study requires a total sample size of 124 participants (62 participants per experimental condition).

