**Methods:**

The study design consists of a two-arm randomized controlled trial with two conditions: FC-SBD or Treatment as usual optimized (TAU-O). Participants will be relatives of patients who meet DSM-5 criteria for SBD. The caregivers` primary outcome measures will be the BAS. Secondary outcomes will be DASS-21, FES, DERS, QoL. The patient’s primary outcome measures will be the frequency of critical incidents with the family member with SBD. Secondary measures will be the INQ, PHQ-9, OASIS. Participants will be assessed at pretreatment, post-treatment, and 6-month follow-up. The intention-to-treat principle will be used when analyzing the data.

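### The total of 124 does not follow from 90 evaluable participants and 30% dropout, which give 129 (130 with equal arms)

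*Protocol article*

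**What the plan says.** The whole calculation stands in one paragraph, under Sample size in the protocol article. The outcome is burden, which the abstract names for caregivers: "primary outcome measures will be the BAS".

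- Effect size: two burden effects are cited. A controlled study of a psychoeducational group for relatives of people with borderline personality disorder is reported as "they found medium effect sizes for burden (d=0.45) at post-test and 12-month follow-up". A meta-analysis is cited "on psychological interventions for bipolar disorder (Burden, g = -.80". The authors appeal to these results and then write "we expect an effect size of 0.60 because the design of this study consists of two experimental groups".
- Error rates and test: "taking into account an alpha of 0.05 and a statistical power of 0.80 in a two-tailed t-test".
- Evaluable number: "We need a sample size of 90 participants (45 relatives per condition) to reach an effect size of 0.60 for burden".
- Loss: "we expect a 30% dropout rate", based on earlier studies of relatives.
- Conclusion, presented as following from that loss: "our study requires a total sample size of 124 participants (62 participants per experimental condition").

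**The concern.** Each input and the final figure are printed, so a reader can redo the chain, and the last step fails. An allowance for 30% loss should leave the 90 evaluable participants that the power calculation calls for. Here it leaves fewer. The recruitment target and the claim of 80% power therefore do not agree with each other, and anyone who relies on either is relying on a figure that the paragraph does not support.

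A lesser matter is the reason attached to 0.60. The number of groups in a design does not fix a standardized mean difference, so the sentence does not tell the reader how 0.60 was reached from the effects cited just before it. Power depends far more on that choice than on the dropout arithmetic.

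**Working it through.** **Inputs**, all from the Sample size section: standardized difference d = 0.60; two-sided alpha 0.05; power 0.80; independent two-sample t-test; equal arms; 30% dropout; stated totals 90 (evaluable) and 124 (enrolled); cited burden effects 0.45 and 0.80 in absolute value.

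**Step 1: reproduce the evaluable number.** The noncentral t calculation for d = 0.60 gives n = 44.59 per arm, so 45 per arm and 90 in total, with power 0.804. The plan's figure reproduces.

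**Step 2: allow for 30% loss.** The formula is N = evaluable / (1 − loss).

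- On the total: 90 / 0.70 = 128.6, so 129.
- Per arm: 45 / 0.70 = 64.3, so 65 per arm and 130 in total.

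**Step 3: look for another route to 124.**

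| Route | Result |
|---|---|
| 90 × 1.30 | 117 (118 with equal arms) |
| Normal approximation instead of the t-test: 88 / 0.70 | 125.7, so 126 (63 per arm) |
| Stated total | 124 (62 per arm) |

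None of these gives 124. The second comes closest, but it contradicts the stated 90 and the stated t-test.

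**Step 4: what 124 supports.**

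- Loss that leaves 90: 1 − 90/124 = 0.274, about 27%.
- Evaluable at 30% loss: 124 × 0.70 = 86.8, or 43.4 per arm.
- Power at d = 0.60: 0.785 with 43 per arm and 0.789 with 43.4 per arm, against 0.804 with 45 per arm.
- Shortfall in enrolment: 129 − 124 = 5, or 130 − 124 = 6 with equal arms.

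**Step 5: the effect size in context.** The midpoint of the two cited burden effects is (0.45 + 0.80)/2 = 0.625, so 0.60 lies inside the cited range and just below its middle. Power of the same t-test with 43 per arm:

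| d | Power |
|---|---|
| 0.45 (controlled study of relatives) | 0.54 |
| 0.60 (planning value) | 0.785 |
| 0.80 (meta-analysis, bipolar disorder) | 0.96 |

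All power figures treat participants as independent. The Study design section says that relatives of the same patient are randomized together. Positive correlation within families would lower power; the article gives no value from which to compute by how much.

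**The case against.** **The gap is small.** It amounts to five or six participants and one to two points of power. That stands, and it limits the weight of the point.

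**Dropouts may not be lost to the analysis.** The loss described is during the treatment program, while Data analyses plans intention-to-treat mixed models with likelihood-based handling of missing data over three time points. Using the baseline score could more than close the gap. If the pre-post correlation were 0.3 to 0.5 (an assumption; the article gives none), a baseline-adjusted comparison with 43 per arm would have power of about 0.82 to 0.89 at d = 0.60, before clustering. This is a fair reason not to worry about the trial's real power on this account. It does not rescue the printed calculation, which rests on a simple t-test and needs 90 evaluable participants.

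**The effect-size rationale.** A reader might infer that the two-groups reason is contrary to the evidence: an active comparator should shrink the difference, yet 0.60 exceeds the cited 0.45, so the trial is underpowered at its own cited burden effect. The documents do not support that reading. The same paragraph cites a second burden effect, 0.80, and bases the expectation on both studies. The clause can equally be read as a discount from 0.80 because both arms receive something. The paragraph does not describe the comparators behind the cited effects, so whether the control here is stronger or weaker than theirs cannot be judged. What remains is that the reason is unclear.

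**Conclusion.** The arithmetic point holds. From 90 evaluable and 30% dropout the total is 129, or 130 with equal arms, and no standard route gives 124. As stated, 124 covers about 27% loss; at 30% loss it gives power of about 0.785 to 0.79 at d = 0.60, just short of the claimed 0.80. This assumes the stated two-sample t-test, equal arms, equal loss in both arms, every dropout missing from the comparison, and no clustering.

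The point about 0.60 is secondary and minor. The value lies between the two cited burden effects, but the sentence does not explain how it was chosen. Quoting power at 0.45 alone would give a one-sided picture.

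**What to change.** Revise the one paragraph under Sample size. Either of two corrections will do:

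1. Keep 124 (62 per arm) and state that it covers about 27% dropout, and that at 30% dropout it gives power of about 0.79 at d = 0.60 under the stated t-test, ignoring the clustering of relatives randomized together. This needs no change to enrolment. The cost is a slightly less favourable power statement.
2. If enrolment allows, correct the total to 130 (65 per arm), which keeps 30% dropout and 0.80 power. The cost is six more participants. The Participants section describes the study as ongoing, with recruitment from November 2021 to May 2022, so this may no longer be practical.

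In either case, replace the clause about two experimental groups with a sentence saying how 0.60 was chosen from the cited 0.45 and 0.80. If sensitivity figures are added, give power at both cited values: about 0.54 and 0.96 with 43 per arm.

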### Participants

Participants will be relatives of patients who meet criteria for SBD [38]. The diagnoses will be carried out by a specialist in psychology, and the sample will be recruited from different centers: the Clinical Hospital from the Valencia University and its Mental Health Services; the PREVI Clinical Center and its three centers in Castellon, Valencia, and Alicante; and associations of relatives of people with mental disorders from Valencia, Murcia, and Zaragoza, from November 2021 to May 2022.Thus it is an ongoing study.

In the case of the patients, the following inclusion and exclusion criteria will be established: 1) fulfill the diagnostic criteria for SBD; 2) be in the process of undergoing treatment or follow-up in one of the recruitment centers indicated; 3) give their agreement to participate in the study in writing by signing the informed consent form; in the case of minors, the consent form must be signed by their parents; 4) The presence of another serious pathology such as psychosis, schizophrenia, intellectual disability, etc. will be an exclusion criterion.

In the case of family members, the following inclusion criteria will be followed: 1) being a family member of one of the patients with a diagnosis of SBD who is undergoing treatment or follow-up in one of the recruitment centers indicated; 2) signing the informed consent. The presence of any pathology that keeps the intervention from being carried out (such as psychosis, schizophrenia, substance dependence, etc.) will be an exclusion criterion.

### Procedure

Family members of patients with SBD will be given the opportunity to participate in the study. Once they have completed the informed consent, an expert clinician will carry out the assessment of each participant to check that the inclusion and exclusion criteria are met, and an independent investigator, unaware of the characteristics of the study, will be contacted to carry out randomization. At all times, for randomization purposes, an experimenter from outside the research team will assign each family member to one of the two study conditions (FC-SBD or TAU-O) using a random number software program. The randomization sequence will be concealed from the clinicians participating in the study. Independent assessors will administer the assessment protocol to the participants without being aware of the experimental condition to which they belong (FC-SBD or TAU-O). Patients will also be assessed before starting the intervention programs for relatives. After the assessment has been completed, all the relatives will start to receive the intervention in the condition to which they have been assigned. In the case of patients, they will participate in their current treatment or care. At the end of the intervention, the assessment protocol will be readministered to both relatives and patients, again by independent assessors, and the same thing will be done at the six-month follow-up.

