### Methods and design

#### Study design

This study is a superiority trial. The study design consists of a two-arm randomized controlled trial (RCT). On the one hand, there will be two conditions: Family Connections (FC-SBD) or Treatment as usual optimized (TAU-O), and family members will be randomized to one of the two groups. Family members will be randomized taking into account that if a patient has more than one family member attending the group, they will be randomized together to be included in the same condition. The effects of the treatment will be measured before starting the group, afterwards, and at the six-month follow-up in order to know whether the effects are maintained in the long term. Figure 1 shows the flow chart. This protocol will follow the CONSORT statement (Consolidated Standards of Reporting Trials, http://www.consort-statement.org) [30, 31] and the SPIRIT guidelines (Standard Protocol Items: Recommendations for Interventional Trials) [32, 33].

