
### Interventions

#### Interventions with family members

##### Family Connections Protocol for Relatives of Patients with SBD (FC-SBD)

The intervention lasts three months and includes 12 sessions with a weekly two-hour group format.

The FC program [23] is divided into six modules:Module 1: Up-to-date information and research on suicide (Epidemiology, frequency, Risk factors, protective factors).Module 2: Psychoeducation on the development of suicide, explanatory theories, available treatments, comorbidity.Module 3: Emotional regulation skills, skills of acceptance, validation, approach, awareness, and to decrease emotional reactivity.Module 4: Skills to improve the quality of relationships in family interactions (letting go of guilt and anger, acceptance skills in relationships).Module 5: Communication skills and effective self-expression.Module 6: Problem management and making safe plans for crisis management.All the modules include practice exercises, video viewing, and homework assignments. In addition, throughout the program, with the aim of increasing social support, the FC-SBD program provides a forum where participants can stay in touch and share common problems and solutions.

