##### Treatment as Usual Optimized Protocol (TAU-O)

Family members in this condition will continue to receive their treatment as usual in their care center of reference. In addition, we will optimize the treatment based on the recommendations of the international guidelines for the treatment of suicide. There will be one three-hour session in group format with the following component:Module 1: Updated information and research on suicide (Epidemiology, frequency, Risk factors, protective factors). Psychoeducation on the development of Suicide, Explanatory theories. Available treatments, and comorbidity.

In both conditions, after each face-to-face session, the participant will be asked to review the contents covered during the session as homework (independently of the homework corresponding to the specific module being addressed). All interventions carried out with family members will be performed by clinical psychologists or general health psychologists with at least a Master's degree or a doctoral degree and previous training in the administration of the programs.

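### The post-treatment assessment is tied to the end of interventions of very different length, so the arms can be compared at different times since randomisation

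*Protocol article*

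**What the plan says.** Three places in the protocol article set the timing, all relative to treatment. The abstract says "Participants will be assessed at pretreatment, post-treatment, and 6-month follow-up". The Study design section says "The effects of the treatment will be measured before starting the group, afterwards, and at the six-month follow-up". The Procedure section gives the operational rule, "At the end of the intervention, the assessment protocol will be readministered to both relatives and patients, again by independent assessors", and adds that "the same thing will be done at the six-month follow-up". None of them counts weeks from randomisation or says where the six months begin.

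The two interventions differ greatly in length. For FC-SBD, "The intervention lasts three months and includes 12 sessions with a weekly two-hour group format". For TAU-O, "There will be one three-hour session in group format", delivered on top of usual care at the relative's own centre, which continues without a stated end.

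Both arms begin at the same point: "After the assessment has been completed, all the relatives will start to receive the intervention in the condition to which they have been assigned".

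The relatives' primary outcome, the BAS, covers the previous six months (Measures - Relatives). So do the items of the critical-incident register, which is the patients' primary outcome.

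**The concern.** A randomised comparison is clean when both arms are measured at the same distance from randomisation. A rule anchored to the end of treatment achieves that only if the treatments last equally long, and here they do not. If TAU-O relatives are reassessed once their session is over, their post-treatment score is close to a repeat of baseline. The FC-SBD score would then reflect the programme plus about three months of whatever else changes with time, including regression to the mean.

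The six-month recall sharpens the problem, because a TAU-O relative questioned soon after the session would report almost entirely on the period before the study.

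The analysis cannot repair this. If time since start is determined by arm, time and treatment cannot be separated in the post-treatment comparison, whether by MANOVA or by the mixed model. TAU-O data not collected near week 12 cannot be reconstructed.

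A smaller matter sits in the same section. The narrative goes from eligibility check to randomisation to administration of the assessment protocol, so it permits the baseline to be taken after allocation.

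**Working it through.** **1. The plan's own figure.** Inputs from Sample size: d = 0.60, two-sided alpha 0.05, power 0.80, t-test, equal arms. The noncentral t calculation, with noncentrality d × √(n/2) and 2n − 2 degrees of freedom, needs 44.6 per arm, hence 45 per arm and 90 in total. At n = 45 the noncentrality is 0.60 × √22.5 = 2.85 and the power is 0.804. The stated 90 is reproduced. It is used below only to set n; the timing point does not depend on it.

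**2. Gap at post-treatment.** Start of intervention = week 0 in both arms.
- FC-SBD: twelve weekly sessions span 11 weeks from first to last; three calendar months are about 13 weeks. The visit falls at about weeks 11 to 13.
- TAU-O: if the end of the intervention means the end of the single group session, the visit falls at about week 0. If it means the end of usual care, no date follows from the text.
- Gap under the first reading: 11 − 0 to 13 − 0 = 11 to 13 weeks.

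**3. Share of the BAS window after the start of treatment.** Six months is about 26 weeks.
- FC-SBD: 11/26 = 42%, 12/26 = 46%, 13/26 = 50%.
- TAU-O, same reading: 0/26 = about 0%.

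**4. Follow-up, by anchor.**
- Six months from the end of each arm's intervention: FC-SBD at 11 + 26 = 37 to 13 + 26 = 39 weeks; TAU-O at 0 + 26 = 26 weeks. The gap is again 11 to 13 weeks.
- Six months from randomisation or another common date: gap 0.

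The text does not choose between these.

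**5. What a time drift could do (illustration).** Assume no treatment effect, and a drift of s SD over about 12 weeks that shows in one arm only. The expected standardised difference is then s, and the chance that a two-sided 5% t-test rejects is its power at d = s:

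| Assumed drift s (SD) | 45 per arm | 62 per arm |
|---|---|---|
| 0.1 | 7.6% | 8.6% |
| 0.2 | 15.5% | 19.7% |
| 0.3 | 29.1% | 38.1% |

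The drift is not in the documents. The calculation treats relatives as independent, as the plan's own calculation does.

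**6. Order of baseline and allocation.** In the Procedure section the eligibility assessment comes first, then the contact with the independent randomiser, then the assessors administering the protocol without knowing the condition, then the start of treatment. Patients are to be assessed before the relatives' programmes begin. Data analyses describes baseline as preceding the intervention. No sentence places baseline before randomisation, and none says that it follows.

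**The case against.** The strongest reply is that the Procedure section describes one reassessment wave for everyone, with no arm-specific schedule, and that TAU-O is more than its added session. Usual care goes on, so nothing says that TAU-O relatives will be reassessed on the day of the session. The flow chart is not available here and may give visit times, and an article may leave visit windows to the full protocol. This stands in part: unequal timing is not shown to be intended, and the end of TAU-O is undefined rather than certainly week 0. It does not dispose of the point. The article states a timing rule, and that rule gives either very different times in the two arms or no time at all in one of them. The Study design section ties measurement to the group, and the TAU-O group meets once.

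The drift figures also draw a fair objection. Their size, their direction and their confinement to one arm are all assumed. Eligibility does not require a recent crisis, so a natural improvement cannot be presumed. About half of the FC-SBD recall window would still precede treatment, which would dampen any drift in the BAS. The table therefore shows sensitivity, not an expected error rate.

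On baseline, the assessors are blinded, and nothing says that relatives know their arm when they answer.

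**Conclusion.** The point holds as a defect in a stated rule. Applied literally, the rule separates the post-treatment assessments by up to about 11 to 13 weeks, on a primary outcome whose recall window would be 42% to 50% post-start in one arm and about 0% in the other. The size rests on reading the end of TAU-O as the end of its session, and on both arms starting at the same point.

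Four stronger conclusions that a reader might draw are not supported:
- That TAU-O will be reassessed at week 0. Continuing usual care leaves that end open.
- That follow-up falls at six months in one arm and nine in the other. This needs an anchor that the text does not give.
- That the bias favours FC-SBD, or that the type I error is 16% to 29%. Improvement over time would favour the arm measured later and worsening would disfavour it; the rates follow only from an assumed drift.
- That baselines are taken after allocation. The order of the sentences permits it, but no sentence says so.

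The timing rule should be corrected because a time confound built into data collection cannot be removed afterwards. The baseline order is secondary.

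**What to change.** State one schedule for both arms, counted from randomisation or from a common cohort start date: post-treatment at about week 12, set to fall after the last FC-SBD session, and follow-up at the same number of weeks in each arm. Give each visit a window and say where the six months begin. Apply the same dates to the patients' assessments. Add a sentence that the relatives' and patients' baseline assessments are completed before allocation is requested.

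If TAU-O relatives are already assessed alongside FC-SBD, this is a change of wording only. If not, TAU-O relatives wait about 12 weeks for their second assessment. Because the article describes the study as ongoing, any TAU-O assessments already made soon after the session should be reported with their dates.
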